## Abstract

**Background:**

The high prevalence of dysphagia among Alzheimer’s disease (AD) patients has become a public health and economic concern. Therefore, effective and accessible dysphagia treatments are needed. As a fundamental rehabilitation of dysphagia, swallowing muscle exercises have received increased attention. Stepwise swallowing training (SST), integrated with all swallowing organs movement, is expected to improve swallowing dysfunction among AD patients. By using a randomized controlled trial design, we propose a multi-center research to evaluate the effectiveness of SST program among AD patients.

**Methods:**

A multi-center exploratory randomized controlled trial, with a 4-week follow-up period, will be conducted in three major public psychiatric hospitals in Guangdong, China. Participants in the control group will be assigned to routine dysphagia care, while participants in the intervention group will undergo the same nursing care and additionally receive the SST program. The SST program includes five sections of swallowing organs training: lip movement, facial movement, tongue movement, mandibular movement, and neck movement. Primary outcomes evaluate the swallowing function, namely, Water Swallowing Test (WTS) and Standard Swallowing Assessment (SSA). Secondary outcomes aim at measuring the improvement of negative impacts of dysphagia, namely eating behavior, ability of daily activity, and nutritional status. Data will be collected at baseline (*T*_1_), at 2 weeks (*T*_2_, intervention), and 4 weeks after intervention (*T*_3_, follow-up).

**Discussion:**

This study will offer trial-based evidence of the effectiveness of SST in relieving dysphagia among AD patients. SST program is expected to improve both the swallowing function and reduce the negative impacts of dysphagia, with an exploration of acceptability in the SST program.

**Trial registration:**

Chinese Clinical Trial Registry, ChiCTR2200056481. Prospectively registered on 6 February 2022.

## Background

Alzheimer’s disease (AD) has become one of the largest global economic burdens. According to the 2015 World Alzheimer’s Disease Report, the total global cost of dementia will increase at the rate of more than 40% between 2015 and 2030—from 818 billion dollars to 2 trillion dollars [1, 2]. However, recent research suggested that China’s domestic socio-economic burden has been overwhelmingly underestimated; this will significantly affect the estimated global cost. In 2015, the cost of AD in China has reached 1.47% of the gross domestic product (GDP), while the worldwide cost accounted for 1.09% of the global GDP, indicating a higher socio-economic cost in AD patients in China. Moreover, the annual cost per AD patient in China was 19 144.36 US dollars (USD), and the annual social and economic cost of AD was 167.74 billion USD, which was 5.95 times higher than the estimated value in the aforementioned report [2]. Additionally, by 2030, a total annual cost related to dementia will reach 50.749 billion dollars [3].

The high socioeconomic burden of AD is mainly due to caregiving demands. Caring for AD patients is highly challenging for their caregivers and family members. The primary difficulty in caregiving is caused by the decline in AD patients’ daily living ability, specifically, the swallowing dysfunction. Clinically, the swallowing dysfunction leads to malnutrition, dehydration, weight loss, fear of eating, and other complications; consequently, it might extend hospital stay and even cause severe injury or death in extreme cases. Swallowing dysfunction or dysphagia, which is a group of clinical syndromes, can cause various diseases. Dysphagia refers to an improper transfer of food from the mouth to the esophagus and the stomach, caused by the impairment of the swallowing organs (e.g., mandible, lips, tongue, soft palate, larynx, esophagus, and so on). Generally, the swallowing process includes the following four physiological stages: oral preparatory, oral, pharyngeal, and esophageal [4].

Significant attention is needed to address the high prevalence of dysphagia in AD patients. Previous studies indicated an incidence rate of 32–45% among mild AD patients with dysphagia and 84–93% among moderate and severe AD patients. Abnormal swallowing function in AD patients manifested as weak tongue movement and pressure, generally occurring in the oral and pharyngeal stages of swallowing. Hence, due to abnormal swallowing function, individuals might exhibit delayed pharyngeal reflex, reduced pharyngeal muscle strength, and food residue after swallowing. Individuals with abnormal swallowing function experience difficulty in forming and pushing the food bolus and, hence, are at high risk of food aspiration [5].

Studies have reported that AD patients with dysphagia at admission are at a higher risk of malnutrition than those without dysphagia, which is associated with the respiratory infection and increased mortality [6]. When screened using the Water Swallowing Test, the incidence rate of malnutrition was 1.67 times higher, with which the severity of dysphagia was positively correlated. Besides, malnutrition also reduces the quality of life in patients [4]. A multi-center cohort study found that swallowing dysfunction was an important cause of pneumonia and lower respiratory tract infection in 170 elderly people in a nursing home (OR = 2.000, 95% CI = 1.2–3.3, *P* = 0.10) [7]. Thus, optimal solutions are urgently needed to improve patients’ swallowing function and living ability.

Dysphagia treatment includes three approaches: compensatory strategies, swallowing rehabilitation, and other approaches. The first aims to reduce the effects of impaired bolus flow to ensure the safety of oral diets [8]; it has many forms, such as postural adjustment, diet modification, swallow maneuvers, and enteral feeding. Changes in head or body posture are recommended to reduce aspiration or residue. Many postural techniques including (but not limited to) head down and lift and side-lying can successfully eliminate aspiration on at least one bolus volume of liquid [9]. Logemann et al. conducted a study using thin liquids with either chin-tuck or nectar-/honey-thickened liquids in individuals with dementia or Parkinson’s disease (PD). Overall, fewer participants aspirated on nectar- (*p*< 0.01) and honey-thickened liquids (*p*< 0.01) [10]. While previous studies are conflicted about these strategies and some data suggest that postural adjustments are inferior to active rehabilitation, other approaches include chemo-denervation, pharmacological treatment, neuromuscular electrical stimulation, and non-invasive brain stimulation [11, 12]. Chemical myotomy and drug application are not highly recommended as first-line treatment in older adults with dysphagia due to the potential risks and side effects.

Wang et al. synthesized 27 randomized controlled trials to explore the effect of noninvasive neurostimulation therapies (repetitive transcranial magnetic stimulation [rTMS], transcranial direct current stimulation [tDCS], and surface neuromuscular electrical stimulation [sNMES]), which work through magnetic or electric fields to trigger and regulate the depolarization of cortical neurons, on dysphagia patients after stroke. A positive effect of rTMS, tDCS, and sNMES was reported in the recovery of swallowing function (standardized mean difference = 0.91; 95% CI: 0.54–1.27; *Z* = 4.84; *P* < 0.00001; *I*^*2*^ = 86%). However, there is no recommended treatment protocol, and for implementation, a specific equipment is required [13].

Swallowing rehabilitation comprises exercises targeted to train specific muscles or muscle groups [8]. Given this development, more evidence-based therapeutic exercises were introduced—instead of centering on an isolated muscle, the training program gradually became more systematic and available. Kim et al. explored the instant effect of simple oral exercise (SOE), performed two times per day for a week, on 84 older adults. Masticatory performance improved immediately by around 16% in the poor-chewing group, and the unstimulated saliva production in all subjects increased to 0.26 ml/min immediately after SOE [14]. Kang et al. examined the impact of a bedside exercise program, which comprised oral, pharyngeal, laryngeal, and respiratory exercises. After implementing the program in 25 stroke patients for 1 h per day for 2 months, the results showed a significant improvement, compared to the control group, in the swallowing function (at the oral phase) and depressive symptoms [15].

However, swallowing exercises, the fundamental rehabilitation for dysphagia, need more high-quality evidence regarding their implementation in AD. Under the neural regulation mechanism of the cerebral cortex sensorimotor, practicing swallowing exercises is effective for dysphagia with stroke/PD or older adults [16, 17]. Clinicians find the implementation of appropriate rehabilitation exercises challenging in patients with AD. In China, clinicians apply swallowing exercises, such as lip lordosis and adduction, mandibular opening and closing, cheek blowing, and tongue extension, generally combined with routine care and other treatments. These exercises can be effective in increasing the flexibility and coordination of swallowing organs and improving the relevant muscles’ strength. Nonetheless, whether swallowing exercises are effective in dementia is controversial. Therefore, simple and feasible swallowing rehabilitation training should be developed for patients with impaired cognition and attention deficit. Based on the current swallowing rehabilitation literature, a multi-center randomized controlled trial will be conducted in three mainland hospitals to investigate the effect of stepwise swallowing training on the function and daily living ability of AD patients.

### Objectives

Based on the literature and clinical evidence, a program has been developed to improve AD patients’ swallowing function and muscle training from top to bottom on lips, tongue, face, and neck. The study aims to evaluate the effectiveness of the Stepwise Swallowing Training (SST) in swallowing function among AD patients with dysphagia.

## Methods

### Trial design

This training program is a multi-center, exploratory, single-blinded, parallel randomized controlled trial (RCT) with a 4-week follow-up period. All stages are conducted according to the SPIRIT reporting guidelines [18]. Treatments administered will be allocated randomly according to a 1:1 ratio by an online random-number generator of SPSS software by research assistants who are not involved in assessment and intervention. The researcher will then offer the research assistants in each hospital the allocation of groups with sequentially numbered opaque, sealed, and stapled envelopes. Then, the training schedule will be conducted based on this research protocol.

### Study settings and participants

This trial will be conducted in three major public psychiatric hospitals in Guangdong, China—Affiliated Brain Hospital of Guangzhou Medical University (GZ), the Third Hospital of Jiangmen (JM), and the Third Hospital of Yuebei (YB). This research has obtained ethical approval from the Institutional Review Board of GZ (approval number: 2021070), and the research will be conducted with the consent of each hospital’s executives. Before allocation, informed consent will be obtained from all participants.

### Inclusion and exclusion criteria

A total of 100 participants of male and female aged above 60 years with AD will be recruited from the three main research institutes. Inclusion criteria are (a) diagnosed as AD by DSM-5; (b) score ≤ 25 on the Mini-mental State Examination (MMSE); (c) score a third-degree or higher on the Water Swallowing Test, demonstrating a risk of aspiration [19]; and (d) have basic communication ability to complete the tests in this trial. Exclusion criteria are (a) swallowing disorders caused by other organic diseases, such as oral disease, esophageal obstruction, digestive tract disease, tumors, or stroke; (b) complications such as other serious somatic diseases that are not suitable for practicing swallowing exercises; and (c) serious impairment in hearing or vision, which may hinder following instructions.

### Interventions

Participants will be randomly allocated to either the SST group or the control group. The flow chart of this study was presented in Fig. 1*.* Participants in the control group will receive routine dysphagia care, while the intervention group will receive SST based on routine care five times a week for four weeks. The process includes five sections of swallowing muscles, and each section will provide step-by-step training, according to the difficulty experienced by the participant. Each section will be divided into three levels of difficulties, starting from level 1(easy) through level 2 to level 3 (difficulty) each time. As presented in Fig. 2, the instructional video will be shown to the patient along with one-to-one guidance.

**Fig. 1 Fig1:**
[figure not shown]
Flow chart of the trial

**Fig. 2 Fig2:**
[figure not shown]
SST flow chart

Moreover, training videos and anime pamphlets will be given to family members and caregivers when participants are discharged from the hospital, and they will be contacted via telephone or WeChat to ensure the training process and measurements.

#### Routine nursing care during intervention

During the intervention and follow-up, participants and their caregivers in both groups will receive routine nursing care and health education about swallowing dysfunction.

#### Concomitant treatments and medication

Routine medications used to control the underlying diseases such as hypertensive and diabetic mellitus will be permitted. Extra benzodiazepines, antipsychotics, and anti-epileptics, which can affect the swallowing function can be taken if necessary. If the participants take medication that might affect their swallowing function, it will be recorded in case report form.

### Outcomes

Study outcomes will be evaluated by trained research assistants who are not aware of group allocation. The time points for measurement will be at baseline (*T*_1_, day 0), 2 weeks after intervention (*T*_2_, day 14), and 4 weeks after intervention (*T*_3_, day 28). The schedule of outcome measurement is presented in Fig. 3.

**Fig. 3 Fig3:**
[figure not shown]
Schedule of outcome measurement

#### Primary outcomes

Water Swallowing Test (WST), a five-level water drinking test, will be used to determine the effectiveness of SST. Evaluators observed individual reactions after drinking 30 ml of water (complete recovery: swallowing without cough; improved swallowing function: occasional choking, and invalid: unchanged or worse swallowing function). Effective rate = (completed recovery + improved swallowing function)/total cases in each group *100%. The sensitivity and specificity of WST ranged from 34.8 to 55.7% and 78.9 to 93.2% in older adults [20].

On basis of WST, Standard Swallowing Assessment (SSA) will be performed to evaluate the severity of dysphagia. The score of SSA ranged from 18 to 46, and a high SSA score reflected serious dysphagia. SSA exhibited a specificity of 0.90 and a sensitivity of 0.97 in detecting dysphagia, with positive and negative predictive values of 0.92 and 0.96 [21].

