### Sample size

The sample size was calculated based on the comparison of WST. By using G*Power 3.1 software, we set a significant difference of 14.2% (74.2% in the experimental group and 60.0% in the control group), an alpha error of 0.05, a beta error of 0.80, and the effect size *f* = 0.32. After calculation, a total sample size of 78 was required. To accommodate for a 20% attrition rate and other confounding factors, we recruited 100 participants. After obtaining informed consent, each involved hospital was allocated to the intervention group or to the control group in a 1:1 ratio.

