### Statistical methods

Exploratory data analysis and Shapiro-Wilk tests will be performed to determine the normality of data distribution. Continuous variables will be expressed as means with standard deviations or medians with interquartile ranges; mean differences will be expressed from baseline to the end of the study. For categorical variables, counts and percentages will be presented, and between-group comparisons at baseline will be tested with the *x*^*2*^ test [25]. Between-group differences at baseline, and in the change from baseline to the end, will be tested with repeated measure analysis of variance. An analysis of covariance will be used to adjust for baseline cognitive functioning. Paired *t*-tests will be performed for between-group comparisons from the baseline to the end. The level of significance will be set as a two-sided *P* value less than 0.05. Data analysis will be conducted using SPSS version 20.0 with intent-to-treat analysis (ITT) and per-protocol (PP) analysis. The results of the ITT analysis will be compared with those of the PP analysis to determine the consistency.

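### The WST effective rate mixes visit states with change from baseline, so its categories leave a gap and may overlap, and no post-baseline method named in the protocol fits this binary rate

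*Protocol article*

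**What the plan says.** **Outcome.** Under Primary outcomes, the "Water Swallowing Test (WST), a five-level water drinking test, will be used to determine the effectiveness of SST". Complete recovery means swallowing 30 ml of water without cough. The other two categories are "improved swallowing function: occasional choking, and invalid: unchanged or worse swallowing function". The summary measure is "Effective rate = (completed recovery + improved swallowing function)/total cases in each group *100"%. No precedence rule is given, and this section names no time point for the rate.

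**Entry.** Under Inclusion and exclusion criteria, participants must "score a third-degree or higher on the Water Swallowing Test, demonstrating a risk of aspiration". The content of the five levels is not described anywhere in the article.

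**Sizing.** Under Sample size, "The sample size was calculated based on the comparison of WST", and "we set a significant difference of 14.2% (74.2% in the experimental group and 60.0% in the control group").

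**Analysis.** Under Statistical methods, "For categorical variables, counts and percentages will be presented, and between-group comparisons at baseline will be tested with the" chi-square test. The other methods named there are repeated-measures ANOVA for between-group differences at baseline and in change to the end of the study, ANCOVA to adjust for baseline cognition, and paired t-tests for comparing the groups from baseline to the end.

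**The concern.** A responder rule has to put every participant in exactly one category. This one classifies two categories by the state at the visit and the third by change since entry. The labels (recovered, improved, not improved) and the descriptors (no cough, occasional choking, unchanged or worse) can then give different answers for the same person. Someone has to decide such cases during the trial or at analysis, and the decision moves the numerator of a primary outcome.

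The rate is a yes/no result per participant and, because it is partly defined by change, it has no value of its own at T1. The one test named for categorical data is restricted to baseline, and the methods named for later visits are made for scores. The quantity that appears to have sized the trial therefore has no matching comparison in the protocol. One method, the paired t-test between arms, is wrong for any outcome in a parallel-group design.

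**Working it through.** **1. The plan's own figure.** Inputs from Sample size are effect size 0.32, "an alpha error of 0.05", and 0.80, printed as a beta error and read here as power. The two-sided level is from Statistical methods.

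- Chi-square with 1 df: N = (1.960 + 0.842)² / 0.32² = 7.849 / 0.1024 = 76.7, so 77, or 78 to split evenly. The stated 78 is reproduced.
- Two-group ANOVA with f = 0.32 needs 80; power at 78 is 0.797.
- Attrition: 78 / 0.80 = 97.5, so 98, rounded up to 100.
- Directly from 74.2% and 60.0%, with mean 67.1%: n per arm = [1.960 × √(2 × 0.671 × 0.329) + 0.842 × √(0.742 × 0.258 + 0.600 × 0.400)]² / 0.142² = 170.7, so 171 per arm, 342 in total.

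The figure of 78 therefore rests on 0.32 and not on the rates printed beside it. That mismatch is a separate matter. Here it means only that the protocol appears to plan on the effective rate, which is the only WST percentage it defines, and does not say so outright.

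**2. The response rule, case by case.**

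| State at T1 | State at T3 | By descriptor | By change | Result |
|---|---|---|---|---|
| More than occasional choking | No cough | Complete recovery | Better | Responder |
| More than occasional | Occasional choking | Improved | Better | Responder |
| More than occasional | Better, still more than occasional | None | Better, so not *invalid* | **No category** |
| More than occasional | Unchanged or worse | None | *Invalid* | Non-responder |
| Occasional | No cough | Complete recovery | Better | Responder |
| Occasional | Occasional, unchanged | Improved | *Invalid* | **Two categories** |
| Occasional | Worse than occasional | None | *Invalid* | Non-responder |

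The third row is a gap in the rule as written. Because the denominator is all cases, such a person counts as a failure by default, which lowers the rate. The sixth row is an overlap and can raise the rate. The last three rows exist only if someone at the third WST degree or above can be described as choking occasionally, and the article does not say.

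**3. Illustration of the overlap.** Assume that the planning rates p are rates under a strict rule, and that the same share q of non-responders in each arm is scored as improved. The observed rate is p + q(1 − p), so the difference becomes 0.142 × (1 − q).

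| q | Control | SST | Difference (points) |
|---|---|---|---|
| 0 | 60.0% | 74.2% | 14.2 |
| 10% | 64.0% | 76.8% | 12.8 |
| 20% | 68.0% | 79.4% | 11.4 |
| 50% | 80.0% | 87.1% | 7.1 |

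The documents give no q, and zero is possible.

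**4. Outcomes against named methods.**

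| Outcome | Chi-square | Repeated-measures ANOVA, ANCOVA | Paired t between arms |
|---|---|---|---|
| SSA score (18 to 46) | Not needed | Usable | Wrong, arms are independent |
| WST grade (five levels) | Named for baseline only | Can be run | Wrong, arms are independent |
| WST effective rate (yes/no) | Named for baseline only | Rate has no T1 value; models are for scores | Wrong, arms are independent |

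**The case against.** The strongest defence is that the labels settle the matter. The category is called improved, and unchanged participants are expressly placed in the failing group, so on an ordinary reading nobody unchanged is a responder. Entry at the third degree or above may also exclude anyone who chokes only occasionally, which would leave the overlap empty. This defence holds as far as it goes. A reader might infer that the rule counts unchanged participants as successes and inflates both rates; the documents do not support that, because neither the level descriptions nor the frequency of such cases is given. If the planning rates came from the same loose rule, any misclassification is already in them and no shrinkage follows. The defence does not close the gap. If the labels govern, the occasional-choking descriptor has no function; if the descriptors govern, a real improvement can go unclassified.

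On the analysis, a reader might infer that the primary endpoint is never validly compared, or that t-tests will be run on a binary rate. Neither is stated. SSA and the WST grade fit the named models, and an article may leave a test for the rate to an analysis plan. That answers the silence on a test for the rate. It does not answer the paired t-test between arms, which is an error in the text itself.

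The trial is also described as exploratory and its assessors are unaware of allocation, so inconsistent scoring would mainly add noise and would not by itself favour an arm.

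**Conclusion.** The concern holds in a limited form. The stated response rule is not exhaustive and may not be exclusive, and it ignores the WST levels that the trial already uses for entry. This follows from the wording and needs no assumption. Its size cannot be determined: the gap lowers the rate, the overlap raises it, and the dilution figures (14.2 points falling to 11.4 at q = 20%, or to 7.1 at q = 50%) rest on an assumed q, equal in both arms, and on planning rates taken as strict.

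No post-baseline method named in the protocol fits the binary rate, and the paired t-test is misassigned for independent arms. That the rate was the sizing endpoint is a reasonable inference and not a stated fact. The analysis of SSA by the ANOVA and ANCOVA models is not affected.

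**What to change.** Settle the following before outcome data are examined by arm:

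1. Define response by change in WST level from T1 to one named time point, with categories that are exclusive and exhaustive. For example, responder = at least one level better, non-responder = same or worse level, with full recovery reported separately. The one-level threshold is a choice for the trial team to justify.
2. Confirm that 74.2% and 60.0% refer to that definition, or restate the planning rates.
3. Compare the arms on the rate with a two-group test of proportions, or with a logistic model adjusted for baseline WST level and hospital. Report a standardised risk difference (averaged from the model's predicted probabilities) with a 95% CI.
4. Replace the paired t-test with an independent-groups comparison.

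The cost is wording in Primary outcomes, Sample size and Statistical methods. No new measurement is needed, provided the five-level grade is recorded at each visit. The downside is that effective rates may move up or down, and may be less comparable with earlier studies that used the loose rule.
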